### 2.2. Recruitment

Treatments are randomly assigned using a computer program. To guarantee allocation concealment, treatments are assigned centrally via the web through Clinapsis^®^, an application designed to assist in the design and management of epidemiological and non-commercial clinical studies Clinapsis® Patients are recruited and screened for eligibility in three consecutive steps. Firstly, the principal investigator of each hospital is thoroughly briefed concerning the inclusion and exclusion criteria of the study, since they provide therapists with the information for possible inclusion. Secondly, the main researcher gives information about the study to potential participants, including the objective and description of the study, the duration, and risks and benefits. If the patients are interested in the study, an appointment is made to provide more detailed information and to answer questions. When the patient agrees to participate in the study, the informed consent is signed before obtaining the medical record, in order to guarantee privacy. Lastly, after obtaining informed consent, the patients are screened by the primary investigator to assure inclusion. 

After group allocation and before starting treatment (T0), pre-intervention tests are performed to assess the baseline values of primary and secondary outcome measures. At week 3, an assessment (T1) of only primary outcomes is performed. Within one day after completing the intervention (T2), data will be collected for all efficacy outcomes (see outcome measures section). The same data will be collected at three months after the end of the intervention (T3), and again at six months (T4). During the five-week intervention period, each session data will be collected regarding intervention adherence (number of sessions and duration), physiotherapy intensity, which exercises were performed for each patient and their incidences. All visits and efficacy assessments are performed at the rehabilitation center where patients have been initially treated for five weeks (whenever possible during routine clinical follow-up visits). Only when the patient is not able to personally attend the site due to a medical condition, the assessment takes place at home.

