All data are recorded on-line using an electronic data form Clinapsis^®^, available from the study coordinating center. All investigators were trained in the use of the application and have a help guide, as well as a consultation service directly with the logistics coordinator of the study. Access to the study database is restricted to authorised study personnel by password.

For the calculation of the sample size, we have assumed that conventional rehabilitation will be associated with a clinically relevant change in the Trunk Impairment Scale at five weeks compared to the baseline. The minimal clinically relevant difference has been established as 3-point [44]. We have also assumed that rehabilitation by CSEs program will add a benefit of 1.6 points at five weeks, equivalent to 10% in the scale. That is, the experimental group with CSE will present a change of 4.6 points at five weeks with respect to the baseline situation (intragroup). Assuming a common standard deviation of 4 [45], and estimating a 10% lost at follow-up, accepting an alpha risk of 0.05 and a beta risk of less than 0.2 in a bilateral contrast, it will be necessary to include 110 patients in each group to detect a difference between groups of 1.6 points or higher on the total S-TIS 2.0 scale. The calculation of the sample size was done with the GRANMO program.

If a patient, either in CG or EG, has to withdraw from the treatment sessions due to a transient disease or mind trauma, he or she may be re-included if the dropout period is shorter than 10 days. Patients are allowed to withdraw from the study for any reason, and no adverse events have been described previously.

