### 2.5. Interventions

The interventions are performed five days a week for five weeks. EG participants receive 12.5 h (30 min per day) of additional core stability exercises (with or without TENS). All individuals will perform conventional physiotherapy (EG:30 min and CG: 1 h). All interventions will be performed by trained experts in neurological physiotherapy with extensive/over five years of experience treating stroke survivors and with a Master’s Degree in Neurology. Before starting the study, a one-day training session was carried out in order to standardise the procedures and provide the physiotherapists with specific training in the CSEs program and TENS by the clinical director. If there are doubts, they can always get in touch with the clinical coordinator and principal investigator. Each centre has a dossier with the program and videotapes of all CSEs and their explanations. In the meeting with all therapists of the different hospitals involved, a protocol for conventional physiotherapy focusing on improving patients’ disabilities was agreed upon.

The follow-up period is not controlled. At this stage, patients will not follow a specific treatment supervised by the research team, i.e., “usual care”, and the duration can also be variable. Patients of experimental and control group may continue to perform CP and/or aerobic-based therapy as prescribed by the responsible physician, or on their own initiative (private physiotherapy) if they wish. In this case, this additional physiotherapy will not be provided in the same rehabilitation unit by the same previous physiotherapist, but in outpatient physiotherapy centers. Conventional therapy and aerobic-based therapy for long term are recorded.

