Secondary outcome measures include: Sitting functional balance is assessed by the Spanish version of Function in Sitting test (S-FIST) [57]. It is a bedside evaluation of sitting balance and functional sitting everyday activities that assess sensory, motor, proactive, reactive and steady balance factors. The S-FIST consists of 14 tested parameters with an ordinal scale (0–4) for each test item, with 0 indicating the lowest level of function and 4 the highest level. Each participant sat at the edge of a standard hospital bed without air mattresses, with the proximal thigh (1/2 femur length) supported by the bed. The bed height was adjusted and a step stool was used if necessary to bring the hips and knees to approximately 90° flexion, with both feet flat on the floor or stool. The higher score is 56 points. Sitting functional balance is evaluated at T0, T2, T3 and T4.Standing balance and risk of falling is evaluated by Berg Balance Scale (BBS) [58,59]. It provides a psychometrically sound measure of balance impairment. It is used objectively determine a patient’s ability (or inability) to safely balance during a series of predetermined tasks. It is a 14-item scale; patients must maintain positions and complete moving tasks of varying difficulty. In most items, patients must maintain a given position for a specified time. Each item consists of a 5-point ordinal scale ranging from 0 to 4, with 0 indicating the lowest level of function and 4 the highest. A score of 56 indicates functional balance. A score of < 45 indicates that individuals may be at greater risk of falling. BBS is assessed at T0, T2, T3 and T4.Postural control is evaluated by the Spanish version of Postural Assessment Scale for Stroke (S-PASS) [60]. It was designed specifically for patients with a stroke, regardless of postural competence. It has two subscales: mobility and balance. The first measures the patient’s ability to change position from lying, sitting and standing, and the second in maintaining stable postures in sitting and standing. The S-PASS consists of 12 items with a 4-point scale, where items are scored from 0–3. The higher score is 36 points, indicating an optimal postural control. It is evaluated at T0, T2, T3 and T4.Lower limb spasticity by Modified Ashworth Scale (MAS) [61]. This tool measures resistance during passive soft-tissue stretching of muscle. It is performed while the assessor moves the hip adductors, knee extensors and ankle plantar flexors in the supine and lateral position. The MAS is assessed at T0, T2, T3 and T4.ADL by Barthel Index (BI) [62]. This shows the degree of independence of a patient from any assistance. It covers 10 domains of function (activities): bowel and bladder control, as well as help with grooming, toilet use, feeding, transfers, walking, dressing, climbing stairs and bathing. The ADL is evaluated at T0, T2, T3 and T4.Health-related quality of life is measured by the Spanish-version of 5-Dimensions Questionnaire (EQ-5D-5L) [63,64]. It is a generic patient’s health-related quality of life measurement with evidence of good reliability and validity in various disease populations, including strokes. Patients chose five levels of severity (1, no problem; 2, slight problem; 3, moderate problem; 4, severe problem; and 5, unable to function/extreme problem) in five dimensions (mobility, self-care, usual activity, pain/discomfort and depression/anxiety), and rated their overall health status via the EQ-VAS. Quality of life is assessed at T0, T2, T3 and T4.Rate of falls is measured by a specific registry created specifically for this study. The outcome is defined as the average number of falls per patient during the intervention period and follow-up. It is recorded at T0 (falls before stroke), T2, T3 and T4.Gait speed is assessed by BTS G-Walk. It is a wireless system consisting of an inertial sensor composed by a triaxial accelerometer, a magnetic sensor and a triaxial gyroscope that was positioned on S1 vertebrae. From the data acquired, the system extrapolates all spatial-temporal gait. The patient walks for one minute without being aided; this variable is only performed if the patient has a 6-point stepping section of BBA.

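### Off-site assessment is limited to medical reasons, so patients who miss T3 or T4 for other reasons have no stated way to give even interview-type outcomes

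*Protocol article*

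**What the plan says.** Section 2.2 sets the default place of assessment: "All visits and efficacy assessments are performed at the rehabilitation center where patients have been initially treated for five weeks". Visits are to coincide with routine clinic appointments where that can be arranged. The single exception follows: "Only when the patient is not able to personally attend the site due to a medical condition, the assessment takes place at home".

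T2 is due within one day of the end of treatment. T3 and T4 follow three and six months after it, at weeks 17 and 29 (section 2.6).

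Section 2.5 leaves the follow-up period uncontrolled and says of any continuing treatment that "this additional physiotherapy will not be provided in the same rehabilitation unit by the same previous physiotherapist, but in outpatient physiotherapy centers".

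In section 2.7, falls, the Barthel Index and EQ-5D-5L are scheduled at T0, T2, T3 and T4, and no mode of administration is given for the Barthel Index or EQ-5D-5L. On falls, the section states "Rate of falls is measured by a specific registry created specifically for this study", then "The outcome is defined as the average number of falls per patient during the intervention period and follow-up", and "It is recorded at T0 (falls before stroke), T2, T3 and T4". For S-FIST it specifies the setting: "Each participant sat at the edge of a standard hospital bed without air mattresses".

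Section 2.8 keeps every randomised participant with a baseline assessment in the main analysis, imputes missing data and explores the impact of doing so. A secondary analysis is restricted to participants who followed the protocol and have no missing data.

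**The concern.** The restriction is a fixed rule, not a detail left unsaid: all assessments are at the centre, and the only way out of the centre is medical. Someone who has moved, lacks transport or does not want to make the journey falls outside it.

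This bears on T3 and T4. By then treatment at the centre has ended and physiotherapy, if any, is given elsewhere. These two visits carry the objective of learning whether effects last, which the introduction lists as a secondary objective and the discussion calls an important goal.

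Willingness and ability to return may depend on function, and patients know their treatment (section 2.3). Data missing for these reasons may therefore be related to outcome and to arm. Imputation does not remove that bias if the missingness depends on function that was not observed. For outcomes obtainable by asking the patient, the gap need not arise.

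**Working it through.** **1. What is lost when a visit is missed for a non-medical reason.**

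| Outcome at T3/T4 | Stated route if the patient does not come | Could an interview plausibly supply it? |
|---|---|---|
| S-TIS 2.0, BBA stepping (primary) | none | no, performance test |
| S-FIST, BBS, S-PASS, MAS, gait speed | none | no, performance test or physical examination |
| Falls | none | yes, a count |
| Barthel Index | none | yes, everyday activities |
| EQ-5D-5L | none | yes, patient-rated |

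The last column is my judgement; the article does not discuss telephone use of these instruments.

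**2. Falls exposure.** Assume that the registry is filled only at visits; the article does not say. The outcome covers the whole 29 weeks.
- T4 missed: weeks 17 to 29 unobserved, 29 − 17 = 12 weeks, 12/29 = 41%.
- T3 and T4 both missed: 29 − 5 = 24 weeks, 24/29 = 83%.
- T3 missed, T4 attended: falls may be recovered, but over a 24-week recall period instead of 12.

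**3. The plan's own allowance for loss.** Section 2.2 gives a difference of 1.6, SD 4, two-sided alpha 0.05, power 80%, and the allowance "estimating a 10% lost at follow-up".
- n per group = 2 × (1.960 + 0.842)² × 4² / 1.6² = 2 × 7.85 × 6.25 = 98.1, rounded up to 99.
- 99 / (1 − 0.10) = 110 per group. The stated figure reproduces.

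This 10% belongs to S-TIS 2.0 at five weeks. It is not a T3/T4 rate and is not divided by cause.

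**4. Precision, as an illustration only.** Let d be the proportion missing at T3 or T4, and assume that half of those patients are reached by telephone. The ratio of standard errors with and without the calls is √[(1 − d)/(1 − d/2)].

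| d (assumed) | Without calls (of 220) | With calls | Ratio | Reduction in SE |
|---|---|---|---|---|
| 10% | 198 | 209 | √(198/209) = 0.973 | 2.7% |
| 20% | 176 | 198 | √(176/198) = 0.943 | 5.7% |
| 30% | 154 | 187 | √(154/187) = 0.907 | 9.3% |

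The gain is small at 10% and modest beyond. Precision is not the main argument.

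**5. Bias.** If a proportion p of an arm is missing and those patients would have scored Δ lower than attenders, the complete-case mean of that arm is too high by p × Δ. The between-arm difference is therefore shifted by p_EG × Δ_EG − p_CG × Δ_CG. The documents give none of these four quantities, so the shift cannot be computed.

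**6. S-FIST at home.** Section 2.2 permits assessment at home; section 2.7 describes S-FIST on a standard hospital bed. A home assessment will not normally meet that description, and the article does not say how such a score is handled.

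**The case against.** The strongest reply is that uniform face-to-face assessment with a medical exception is a defensible choice, and that the most outcome-related misses are already covered: a patient too disabled by stroke to travel plausibly qualifies for a home visit. That largely stands. What remains is relocation, logistics and reluctance, for which the article gives no rate.

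It can also be said that retention procedures belong in a full protocol. That would answer a silence, but here the article states a restrictive rule.

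Several stronger readings are tempting and are not supported:
- *A patient who misses a visit loses every outcome.* Loss is per visit. Other visits count, the patient stays in the main analysis population, and missing values are imputed. Falls may be picked up later.
- *T2 is equally exposed.* T2 falls within one day of the last session, so patients who complete treatment have little exposure. The endpoint used for sample size is little affected.
- *Gait speed cannot be measured at home.* The sensor is described as wireless and body-worn, and nothing ties it to the hospital.
- *The bias is large against the Barthel benchmark.* With an assumed 10-point gap and assumed losses of 7% and 13%, the shift would be 10 × (0.13 − 0.07) = 0.6 points. Each input is invented, the figure is for complete cases while the main analysis imputes, and the discussion's benchmark of about 2 points does not state its scale. If the range were 0–20, the same shift would be 0.6 × 20/100 = 0.12. The comparison should not be used.

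Finally, telephone collection mixes modes in unblinded patients and cannot recover the primary outcomes. Both points are true and limit the benefit.

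**Conclusion.** The point holds as a modest weakness in data collection at T3 and T4. The rule leaves patients who stay away for non-medical reasons with no stated route to contribute falls, Barthel Index or EQ-5D-5L. The resulting gaps are avoidable and may be informative for the sustainability objective.

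No bias figure can be given, because the documents give no rate of such misses. The standard-error gain of 2.7% to 9.3% assumes a loss of 10% to 30% with half of those patients reached. The conclusion also rests on the premise that the three outcomes can be taken by interview, which is reasonable but not stated in the article.

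No stated figure is wrong. The one mismatch within the text is between the home route and the S-FIST setting. The case for change is that it is cheap and that outcomes not collected at the scheduled date may not be recoverable later.

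**What to change.** Add to section 2.2, after the sentence on home assessment: when a patient who has not withdrawn from the study does not attend T3 or T4 for any reason, and no home visit takes place, the existing blinded assessor collects falls since last contact, Barthel Index and EQ-5D-5L by telephone at the scheduled date. Mode and place of assessment are recorded for every visit. Performance tests stay face to face.

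Reconcile sections 2.2 and 2.7 on S-FIST: state how it is handled when no hospital bed is available, and flag scores obtained at home.

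Cost: one protocol sentence, a telephone script, two data fields and some assessor time. The downside is a possible mode effect, expected to be small, on three secondary outcomes. A sensitivity analysis that leaves out telephone records can check it. Missing T3/T4 values of the primary outcomes and other performance tests still depend on imputation.

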#### Patient and Public Involvement Subsection

Patients and the public were not involved in any way in the co-production of this research.

### 2.3. Blinding

Due to the nature of the interventions, the study has a single-blind design. Therapists and participants cannot be blinded to treatment allocation. To avoid detection bias, efficacy outcomes are evaluated by an independent assessor blinded to the intervention. Each center has a therapist evaluator. They had a training day by principal investigator for the correct use of scales and questionnaires. This information is available online and in the paper. Furthermore, statistical analysis will be conducted, blinded to the allocation.

### 2.4. Selection Criteria 

Patients will have to meet the following eligibility criteria to be included in the study.

Inclusion criteria

First ever-stroke ≤ 30 days (diagnostic criteria according to the World Health Organisation definition; corresponding to ICD-9 code 434) whether cortical or subcortical, and ischemic or hemorrhagic.Unilateral localisation of the stroke verified by computed tomography; if a patient shows previous problems, but does not have any neurological or clinical impairment, he/she would be included in the study.Both sexes and age ≥ 18 years old.Ability to understand and execute simple instructions.Impairment of sitting balance assessed by the Spanish Version of Trunk Impairment Scale.2.0 (S-TIS 2.0) ≤10 points [46,47].Severity of stroke by the Spanish National institute of Health Stroke Scale (S-NIHSS) [48] score ≥ 2 points.

Exclusion criteria

Modified Rankin Scale [49] > 2 points before stroke.Concurrent neurological disorder (e.g., Parkinson’s disease) or major orthopedic problem (e.g., amputation) that hampers sitting balance.Relevant psychiatric disorders that may prevent from following instructions.Other treatments that could influence the effects of the interventions.Contraindication to physical activity (e.g., heart failure).Use of cardiac pacemakers.Patients with hemorrhagic strokes that have undergone surgery for intracranial decompression.Patients whose stroke occurs exclusively and only in the cerebellum and brainstem. Patients whose main stroke is localised on another area and who also have a small lesion in the cerebellum and brainstem would not be excluded.

### 2.5. Interventions

The interventions are performed five days a week for five weeks. EG participants receive 12.5 h (30 min per day) of additional core stability exercises (with or without TENS). All individuals will perform conventional physiotherapy (EG:30 min and CG: 1 h). All interventions will be performed by trained experts in neurological physiotherapy with extensive/over five years of experience treating stroke survivors and with a Master’s Degree in Neurology. Before starting the study, a one-day training session was carried out in order to standardise the procedures and provide the physiotherapists with specific training in the CSEs program and TENS by the clinical director. If there are doubts, they can always get in touch with the clinical coordinator and principal investigator. Each centre has a dossier with the program and videotapes of all CSEs and their explanations. In the meeting with all therapists of the different hospitals involved, a protocol for conventional physiotherapy focusing on improving patients’ disabilities was agreed upon.

The follow-up period is not controlled. At this stage, patients will not follow a specific treatment supervised by the research team, i.e., “usual care”, and the duration can also be variable. Patients of experimental and control group may continue to perform CP and/or aerobic-based therapy as prescribed by the responsible physician, or on their own initiative (private physiotherapy) if they wish. In this case, this additional physiotherapy will not be provided in the same rehabilitation unit by the same previous physiotherapist, but in outpatient physiotherapy centers. Conventional therapy and aerobic-based therapy for long term are recorded.

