The primary objective of this study is to evaluate the effectiveness of CSEs protocol (with and without TENS), in addition to conventional physiotherapy (CP) to improve dynamic sitting balance and gait (stepping) at short/mid-term in the subacute phase of a stroke. Secondary objectives are to evaluate the effectiveness of CSEs (with and without TENS) in addition to CP to improve postural control, standing balance, fall rate, risk of falls, gait speed, lower limb spasticity, ADL and QoL. Another secondary objective is to explore the sustainability of the effects of CSEs over time. It is important to know whether the treatment effects are sustainable over time, or if continuous therapeutic input is necessary to maintain the level of function even after being discharged (home).

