### 2.8. Statistical Analysis

The main analysis population will be defined by intention-to-treat, comprising all randomised participants with a baseline assessment, regardless of later events such as protocol violations, missing data or loss to follow-up. Missing data will be imputed and the impacts of imputation on results will be explored. Secondary analyses will be conducted, restricted to the population of participants who followed the study protocol and had no missing data.

General linear models with repeated measures design will be used to test the effect of the Core Stability program (with or without TENS) on the change in the outcome of interest (total S-TIS 2.0 score or any other outcome) between the baseline and follow up (five weeks), using a repeated measures design with two levels (baseline, five weeks), as well as a two-level factor testing the intervention (usual care). The models will adjust for clinically relevant covariates, such as site, age, baseline levels of the dependent outcomes or severity of stroke. Similar models will be built to explore the effect of Core Stability at different time points (three months; six months). Similar models will test the effect of TENS added to Core Stability on primary and secondary outcomes, as well as primary and secondary endpoints.

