A decrease in gait velocity and double support time could represent an attempt at increasing postural stability to reduce fall risk [69]. Specifically, decreased velocity may reduce the body’s momentum, increasing the likelihood of recovering from a loss of balance. A walking speed of 0.8 m/s is predictive of weak functional abilities, while a speed of 0.6 m/s establishes a threshold below which the risk of falling is critical [77]—the minimally clinically important difference in stroke patients (0.6; 0.8 m/s) [78]. 

One of the first objectives of rehabilitation in the subacute phase of the stroke is to achieve optimal trunk control and dynamic balance while sitting. The proposal of this study is to achieve this by training the core muscles. This results in a better balance in sitting, standing, and in a more efficient gait [79]. The earlier these patients can be autonomous, the less time they will be inactive [80], and in this way the adverse effects of immobilisation can be reduced [81]. Additional trunk rehabilitation is beneficial in improving gait performance in sub-acute stroke [82]. Therefore, if the results of this study are positive, we recommend to incorporate these exercises as early as possible in a stroke rehabilitation program. 

Another important goal of this study is to discover whether the treatment effects are sustainable over time, or if the continuous therapeutic input is necessary to maintain the level of function even after the discharge home [83]. In our knowledge, there is no systematic review about the long-term effects of core stability exercises on improving balance and gait in a stroke subacute phase.

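### The planned models test for an effect at three and six months but give no inference on its change since week 5, and the design cannot show whether continued therapy is needed

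*Protocol article*

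**What the plan says.** The objectives at the end of section 1 (Introduction) include: "Another secondary objective is to explore the sustainability of the effects of CSEs over time". The next sentence explains why: to learn whether effects last "or if continuous therapeutic input is necessary to maintain the level of function even after being discharged". Section 3 (Discussion) presents the same pair as an important goal of the study, namely to "discover whether the treatment effects are sustainable over time, or if the continuous therapeutic input is necessary to maintain the level of function".

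Section 2.8 describes the main analysis as a general linear model "using a repeated measures design with two levels (baseline, five weeks" and a two-level intervention factor. For later visits it says: "Similar models will be built to explore the effect of Core Stability at different time points (three months; six months". It names no comparison of a later visit with week 5.

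Section 2.5 states "The follow-up period is not controlled". After week 5, patients in either arm may have conventional or aerobic-based therapy, prescribed by their physician or arranged privately, for a variable time. This therapy is recorded, but section 2.8 gives it no role in the analysis.

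**The concern.** Sustainability is about change: is the between-arm effect at week 17 or week 29 smaller than at week 5? A model that compares one later visit with baseline answers a neighbouring question, whether an effect is present at that visit. If only visit-by-visit results are available, readers will tend to compare p-values. An effect that is significant at week 5 and non-significant at week 29 is then easily taken as lost, although that pattern can arise by chance when nothing has changed.

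The second half of the goal has a design problem. Later therapy is not assigned, and it probably depends in part on how the patient is doing. Patients who continue therapy and patients who stop are therefore not comparable groups, and no sample size repairs that. At stake is a conclusion, in either direction, about the need for therapy after discharge that the trial cannot support.

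**Working it through.** **Inputs from the protocol article (section 2.2).** Difference 1.6 points on S-TIS 2.0 at five weeks, common SD 4, two-sided alpha 0.05, power at least 80%, 10% loss, 110 per group.

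**Assumptions not in the document.** The same true effect (1.6), SD (4) and number of completers (99 per arm) at weeks 5 and 29; correlation r between a patient's week-5 and week-29 changes from baseline of 0.5 to 0.85.

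**1. The plan's own figure.** n = 2 × 4² × (1.960 + 0.842)² / 1.6² = 98.1, rounded up to 99 per group; 99 / 0.90 = 110. The stated sample size reproduces, so nothing here rests on an error in it.

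**2. What separate models provide.** With complete data and unadjusted means, (arm difference in T4−T0) − (arm difference in T2−T0) = arm difference in T4−T2. The point estimate of the change in effect therefore follows by subtraction. Its standard error does not, because it depends on r, which models fitted one visit at a time do not supply.

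**3. How often p-values diverge with no loss of effect.** SE of an arm difference = 4 × √(2/99) = 0.569. Expected z = 1.6 / 0.569 = 2.81. Probability of significance at one visit = 0.804. Treating the two z-statistics as bivariate normal with correlation r:

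| r | Significant at week 5, not at week 29 (all trials) | Same, among trials significant at week 5 |
|---|---|---|
| 0.5 | 11.2% | 11.2 / 80.4 = 13.9% |
| 0.7 | 8.6% | 8.6 / 80.4 = 10.7% |
| 0.85 | 6.1% | 6.1 / 80.4 = 7.6% |

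**4. Example at r = 0.7.** Suppose the estimates are 1.6 at week 5 and 1.0 at week 29. The 95% CI at week 29 is 1.0 ± 1.96 × 0.569 = −0.1 to 2.1, which looks like a lost effect. The change is 1.0 − 1.6 = −0.6. Its SE is 4 × √(2 × 0.3) × √(2/99) = 0.44, so its 95% CI is −1.5 to 0.3. The data show neither loss nor maintenance.

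**5. What the direct contrast can deliver.** SE = 4 × √(2(1−r)) × √(2/99).

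| r | SE | 95% CI half-width | Power, full loss (1.6) | Power, half loss (0.8) |
|---|---|---|---|---|
| 0.5 | 0.57 | 1.11 | 80% | 29% |
| 0.7 | 0.44 | 0.86 | 95% | 44% |

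**6. Continued therapy.** No calculation can settle this part; the passages have to be set side by side. The Introduction and Discussion pose the need for continued input as something the trial will inform, while section 2.5 leaves that input to physician and patient. As a purely assumed illustration of its influence, a between-arm difference in uptake of 10 to 30 percentage points with a benefit of 1.6 points per user would move the week-29 arm difference by 0.10 × 1.6 = 0.16 to 0.30 × 1.6 = 0.48 points.

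**The case against.** A reader might infer that the sustainability objective cannot be answered at all. The documents do not support that. The objective is only to explore, and a randomised comparison at three and six months validly shows whether an effect is still present. Uncontrolled usual care does not break randomisation for that question, and openly describing follow-up as uncontrolled is not an error.

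A reader might also infer that the change in effect is never estimated. That too goes too far: step 2 of the working shows that the point estimate is available and only its precision and test are missing. Nor does section 2.8 say outright that each later visit gets its own two-level model. That is the natural reading of its reference to similar models, but not the only one, and an SAP that is not shown could add the contrast.

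A third tempting claim is that control patients catching up through outside therapy would make the effect look lost when it is not. If the T3/T4 effect is that of the programme followed by usual care, such catching up is a real fall in the between-arm effect.

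It is also fair that the divergence in step 3 is the ordinary type II error of about 20% at any one visit, that the article states no rule of reading p-values side by side, and that no causal analysis of continued therapy is planned.

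Two things stand. The model form as stated gives no inference on change since week 5, which is what the objective concerns. And the Discussion, not only a sentence of rationale, makes the need for continued input a goal.

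**Conclusion.** The point holds in a limited form. As written, the analysis can say whether a between-arm effect is present at weeks 17 and 29 under usual care; it cannot say with stated uncertainty how far that effect has moved since week 5. The need for continued therapy lies outside what the design can show, and recording that therapy permits description only.

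The risk of a misleading pattern is modest: 8% to 14% of trials significant at week 5, or 6% to 11% of all trials. These figures depend on the assumed constant effect, SD, completers and correlation, none of which the article gives for week 29. The sample size, the week-5 analysis and the randomised comparisons at later visits are unaffected. This is an inexpensive improvement to an exploratory objective that should be made.

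**What to change.** 1. Fit one longitudinal model per outcome with all post-baseline visits (T1 to T4 for the primary outcomes; T2 to T4 for secondary outcomes measured at those visits), the baseline value as covariate and arm-by-visit terms. Report the between-arm contrasts T3−T2 and T4−T2 with 95% CIs as the exploratory estimates of sustainability.
2. Define the T3 and T4 effects as those of the five-week programme followed by usual care, without adjustment for later therapy.
3. Tabulate the follow-up therapy already recorded, by arm.
4. In the Introduction and Discussion, drop the claim about whether continued input is necessary, or label it descriptive and non-randomised.

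The cost is SAP and objective wording plus a little more analysis; no new data are needed. The downsides are losing the causal statement about continued therapy and the limited precision of the contrast. With power for loss of half the effect at only about 29% (r = 0.5) to 44% (r = 0.7), the contrast should be read by its confidence interval and not as a yes/no test.
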